### Statistical analysis

The primary outcome variable will be analyzed with chi-square for comparison of dichotomized GOSE (favorable vs unfavorable) between intervention and sham. The second outcome measures for GOSE at 1 and 6 months after stimulation will be calculated in the same way as for the primary outcome measures. The results of the scales of DAI severity (Gennarelli’s), Adams, and Marshall will be compared with the results of the sham group with the Mann-Whitney *U* test. The second outcome measures related to hemodynamic evaluation will be analyzed with the *t* test for means and SD comparison of 1, 3, and 6 months with the basal value before stimulation.

The median and interquartile range will be calculated for age, intensive care unit days, hospitalization days, and days of treatment of infection. Gender, handedness, level of schooling, mechanism of injury, type of accident, sedation, pupils and presence of dysautonomia, presence of infection, and site of infection will be presented as absolute frequency, proportion, and confidence interval. The Glasgow Coma Scale score will be divided into four categories (3–5, 6–8, 9–12, 13–15) and will be expressed as absolute frequency, proportion, and confidence interval at four moments (scene, admission, discharged from ICU, and discharge from hospital).

Statistical Package for the Social Sciences software version 23.0 for Windows (Prentice Hall, Chicago, IL, USA) will be used for analyzing data. A significance level of *p* < 0.05 will be considered for data analysis.

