**Methods/design:**

This is a double-blinded, randomized, controlled trial of patients with diffuse axonal injury (DAI) due to a severe TBI in an acute stage (less than 8 h). Thirty two patients will be randomized to active coil helmet and inactive coil (sham) groups in a 1:1 ratio. The protocol includes 18 sessions of transcranial LED stimulation (627 nm, 70 mW/cm^2^, 10 J/cm^2^) at four points of the frontal and parietal regions for 30 s each, totaling 120 s, three times per week for 6 weeks, lasting 30 min. Patients will be evaluated with the Glasgow Outcome Scale Extended (GOSE) before stimulation and 1, 3, and 6 months after the first stimulation. The study hypotheses are as follows: (1) transcranial LED therapy (TCLT) will improve the cognitive function of DAI patients and (2) TCLT will promote beneficial hemodynamic changes in cerebral circulation.

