### Secondary outcome measures

Improvement effects of TCLT in follow-up images will be measured by the Marshall computed tomography scale and Adams grading scale for DAI. The hemodynamic improvement effect of TCLT will be measured by transcranial Doppler (systolic and diastolic velocities of the left middle cerebral and basilar arteries, and pulsatility index and resistance index values).

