## Methods/design

### Study design

This study is a sham-controlled, randomized, single-center trial where data will be collected from patients admitted in the emergency service of University of São Paulo General Hospital, São Paulo, Brazil. The recruitment period started in October 2017, and the estimated data collection conclusion is October 2018.

The present trial will respect CONSORT (Consolidated Standards of Reporting Trials) guidelines and SPIRIT (Standard Protocol Items: Recommendations for Interventional Trials) guidelines as shown in Fig. 1 and Additional file 1, respectively.

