#### Secondary

Improvement in early and delayed functional outcomes measured by the GOSE after 1 and 6 months of the first stimulation.Improvement effects of TCLT in follow-up images measured by the Marshall computed tomography scale [60], the Adams grading scale [58], and Gennarelli’s clinical severity scale [44] for diffuse axonal injury.Hemodynamic improvement effect of TCLT measured by transcranial Doppler (systolic and diastolic velocities of the middle cerebral (MCA) and basilar arteries (BA) and the pulsatility index and resistance index values) [44]. It will be evaluated before stimulation and 1, 3, and 6 months after the first stimulation.

For GOSE 1 and 6 months after the first stimulation, a similar calculation of the primary variable outcome will be used.

Patients will repeat the CT scan and the MRI after 1 month of treatment, and they will be evaluated again for the following scales: Gennarelli’s, Adams’, and Marshall’s, and a comparison with image findings of the sham group will be performed.

The transcranial Doppler will analyze systolic and diastolic velocities of the MCAs and BAs and pulsatility index and resistance index values. The means and standard deviation will be calculated for these variables and compared with the first evaluation before stimulation.

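### The transcranial Doppler outcome is compared with the pre-stimulation value and not with sham, so as written the second study hypothesis has no randomised test

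*Protocol article*

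**What the plan says.** The Abstract (Methods/design) lists two hypotheses. The second is that "TCLT will promote beneficial hemodynamic changes in cerebral circulation". Under Secondary outcome measures the Doppler endpoint is again worded as an effect of treatment: "The hemodynamic improvement effect of TCLT will be measured by transcranial Doppler". Study design describes the setting in which these claims are to be tested: "This study is a sham-controlled, randomized, single-center trial".

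The analysis of this endpoint is given in two places:

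- Statistical analysis: a t "test for means and SD comparison of 1, 3, and 6 months with the basal value before stimulation".
- Outcome variables, Secondary: "The means and standard deviation will be calculated for these variables and compared with the first evaluation before stimulation".

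The other outcomes are handled differently in the same sections. The primary analysis is a "comparison of dichotomized GOSE (favorable vs unfavorable) between intervention and sham". The Gennarelli, Adams and Marshall results "will be compared with the results of the sham group with the Mann-Whitney" U test. For the imaging scales, the Secondary section adds that "a comparison with image findings of the sham group will be performed".

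**The concern.** A claim about what the therapy does to cerebral blood flow needs a contrast between patients who received it and patients who received sham. The stated test contrasts later readings with earlier readings. It therefore sets aside the randomised control for this endpoint.

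The setting makes this a practical problem. The first reading is taken in the acute stage of severe brain injury and the later ones at 1, 3 and 6 months. Haemodynamic change over that period without any treatment effect is plausible, and it would occur in both arms. A significant change from baseline could then be credited to the therapy. Setting a significant result in the active arm beside a non-significant one in the sham arm does not repair this, because that comparison is not a test of the difference and does not hold its error rate at 5%.

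**Working it through.** **1. Is a between-arm Doppler test stated anywhere?**

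| Outcome | Comparator in Statistical analysis | Comparator in Outcome variables, Secondary |
|---|---|---|
| GOSE | sham | as for the primary outcome |
| Gennarelli, Adams, Marshall | sham | sham |
| Doppler velocities and indices | value before stimulation | value before stimulation |

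No other section supplies one. The text does not say whether the t test is run within each arm or with the arms pooled. Neither reading estimates active minus sham.

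**2. The plan's own figure.** The article gives no sample size for the Doppler endpoint. Its one calculation (Sample size calculation) is for the primary outcome: chi-square, effect size 0.5, alpha 5%, power 80%. With 0.5 taken as the chi-square effect size w, N = (1.960 + 0.842)² / 0.5² = 31.4, rounded up to 32. This reproduces the stated 32, or 16 per arm, and power at 32 is 80.7%. The arm size of 16 is used below.

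**3. How often the planned test is significant with no treatment effect.** Let δ be the natural change common to both arms, in SDs of the change score. The article does not give δ, so a range is shown. The test is taken as two-sided at 0.05, because sidedness is not stated.

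- Paired t test in n patients: P(|T| > t₀.₉₇₅,ₙ₋₁), where T is non-central t with n−1 degrees of freedom and non-centrality δ√n. Example: n = 16, δ = 0.5 gives non-centrality 0.5 × 4 = 2.0, critical value 2.131, probability 0.465.
- Active arm significant and sham arm not: p(1−p), where p is the one-arm probability. Example: 0.465 × 0.535 = 0.249.
- Between-arm two-sample t test on change: a common δ cancels, so the rate is 0.05.

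| δ | Active arm, n = 16 | Arms pooled, n = 32 | Active significant, sham not | Active versus sham |
|---|---|---|---|---|
| 0 | 5% | 5% | 5% | 5% |
| 0.2 | 12% | 20% | 10% | 5% |
| 0.3 | 20% | 38% | 16% | 5% |
| 0.5 | 46% | 78% | 25% | 5% |
| 0.8 | 85% | 99% | 13% | 5% |
| 1.0 | 96% | >99.9% | 4% | 5% |

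A simulation (40,000 replicates at δ = 0, 0.5, 0.8 and 1.0) gave 5.0%, 46.8%, 84.8% and 96.2% for the active-arm test, and 5.0% to 5.2% for the between-arm test. If only 12 patients per arm supply follow-up Doppler (an assumption), the one-arm rates at δ = 0.2, 0.3, 0.5 and 0.8 are 10%, 16%, 35% and 71%.

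**4. Number of tests.** There are four parameters (systolic velocity, diastolic velocity, pulsatility index, resistance index) and three times. With both middle cerebral arteries and the basilar artery, as in the Transcranial Doppler section, that is 4 × 3 × 3 = 36. With the left middle cerebral and basilar arteries only, as in Secondary outcome measures, it is 4 × 2 × 3 = 24.

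**5. What a between-arm test can detect.** For a two-sample t test on change, 16 versus 16, the non-centrality is d√8 with 30 degrees of freedom. Power is 28%, 59% and 78% for true differences of 0.5, 0.8 and 1.0 SD of change. The difference detectable with 80% power is about 1.02 SD.

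**The case against.** The strongest reply is that a group comparison was probably intended and badly worded. The trial is sham-controlled, the Doppler examiner is blinded to group, and a journal article condenses the full plan. The intention may well have been sound. But the article does state a test and a comparator for this endpoint, twice, while neighbouring sentences name sham for the other outcomes. That is a choice put in writing, not a detail left out.

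Other points limit the size of the problem and are accepted:

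- The natural change is assumed. Entry requires a Doppler with no signs of intracranial hypertension, so an abnormal baseline that later normalises cannot be taken for granted. At 0.2 SD the one-arm rate is 12%, not 46%.
- All 16 patients per arm may not be examined at every visit. Fewer patients lower the one-arm rates, as shown for 12.
- The article does not say how a significant change would be interpreted. It could be credited to the therapy; nothing says that it would be. If sham were used informally, as active significant and sham not, the false-claim rate peaks at about 25%.
- The endpoint is secondary. The primary GOSE analysis is between arms and is unaffected.

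None of these supplies the missing comparison.

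**Conclusion.** The concern holds. As written, one of the trial's two declared hypotheses has no test that uses the randomised comparison, and this is so whether the t test is read as within-arm or pooled. The conclusion rests on the text alone.

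The size depends on natural change, which the article does not give. For an assumed common change of 0.2 to 0.8 SD, the chance of a significant result with no treatment effect is 12% to 85% in the active arm (n = 16) and 20% to 99% with arms pooled (n = 32). These figures assume normally distributed changes, complete follow-up and two-sided testing at 0.05, and apply to each of up to 36 tests. The analysis must be corrected before unblinding. The primary conclusion does not depend on it.

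**What to change.** In Statistical analysis, replace the before-after t test with an active-versus-sham comparison of each Doppler variable: ANCOVA of the follow-up value on arm and baseline value, or one mixed model over the follow-up visits with arm, visit, arm-by-visit and baseline. Report the adjusted difference with its 95% confidence interval, and give within-arm change as description only. Change the matching sentence under Outcome variables, Secondary. It would help, though it is optional, to name one parameter, artery set and time as the main haemodynamic endpoint and label the rest exploratory.

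Two inconsistencies should be reconciled at the same time, because the model depends on them:

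- **Visits.** The Transcranial Doppler section has examinations before the first and after the last stimulation. The Secondary and Statistical analysis sections have 1, 3 and 6 months.
- **Arteries.** Secondary outcome measures names the left middle cerebral artery. The Transcranial Doppler section names both sides.

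The cost is a few sentences, with no extra patients and no data beyond the Doppler readings planned for 1, 3 and 6 months. The price is precision. The trial was not sized for this endpoint, so the article should say that only a large difference, about 1 SD of change, would be detected with 80% power by a between-arm t test on change.

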### Ethical issues

This research involves a minimal risk to the patients, considering that transcranial LED stimulation is a neuromodulation technique tested in other studies [66–69] and with other proposals without severe adverse events reported.

## Discussion

This study protocol is designed to focus on investigating the neuromodulation role of transcranial LED therapy (TCLT) for patients who are victims of severe traumatic brain injury (TBI) with diffuse axonal injury. The objective of the study is to verify the hypothesis that this therapy presents pro-cognitive effects for rehabilitation.

Different studies have emerged to prove the positive effect of TCTL for neuropsychological diseases. After these results, some studies, most of which are case series [66–68], have approached the effects of this treatment for TBI with interesting results.

No specific clinical trials on intervention in the acute stage of TBI were found, which justifies the need for an investigation of the efficacy and effectiveness of TCLT. Considering the global impact of TBI on public health policies, the idea of a non-invasive therapy which helps in neurorehabilitation has an interesting appeal.

The first animal model described with TBI treated with TCLT (808-nm NIR/red LED) was performed with mice. Mice were submitted to only one TCLT section for 4 h. An important reduction (about 90%) of post-injury area size was noticed. Neurological severity scores were also significantly lower at 28 days for laser-treated mice [66]. A different approach with a 6-min daily TCLT session for 10 days reverted deficits in working memory tests of mice [67].

A two-case study with TCLT performed to improve cognitive function in chronic mild TBI patients found improvements in verbal learning, executive function, and memory [68]. With a higher number of patients with chronic mild TBI, the same author published positive results for 11 patients submitted to 18 outpatient sessions, starting at 10 months to 8 years post-TBI. In this study, each LED cluster head (5.35-cm diameter, 500 mW, 22.2 mW/cm^2^) was applied for 10 min to each 11 scalp placement (13 J/cm^2^). They evidenced improvements in executive function as well as sleep and fewer post-traumatic stress disorders [69].

Increasing the number of sessions, another series of two patients submitted to 18 red/NIR TCLT treatments (500 mW, 22.2 mW/cm^2^, 22.48 cm^2^ per treatment area) in chronic TBI patients (who began TCLT at 10 months to 8 years post-TBI) showed improvements in cognition (mainly executive function and verbal memory) [68].

Moderate TBI patients were treated with a high-power NIR laser (10–15 W at 810 and 980 nm) through 20 NIR applications over a 2-month period. They showed decreased headache, depression, anxiety, and insomnia, whereas cognition and quality of life improved, accompanied by changes in the SPECT imaging [70].

After 18 TCLT treatments (26 J/cm^2^ per LED cluster head placement red/NIR, 500 mW, 22.2 mW/cm^2^) in left-hemisphere stroke patients with chronic aphasia, resting-state fMRI scans have been obtained and shown significant increases in “naming ability” [10].

The 3-month period was chosen for the primary outcome because it presents an important relationship with the first year’s outcome. The usual result expected for severe TBI patients is about 30% of favorable outcome at 3 months [71]. Considering a strong size effect for the intervention, we expect a treatment effect of 50 percentage points (difference in the favorable-outcome rate of 30% vs 75%).

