### Radiological features of DAI and clinical presentation

Recent data accepted that diffuse axonal injury (DAI) is now one of the most common types of primary lesions in patients with severe head trauma [5]. DAI not accompanied by an intracranial mass lesion occurs in approximately 50% of patients with severe TBI and causes 35% of all TBI deaths [6].

Patients with DAI present with important impairment of consciousness from the moment of trauma [7]. DAI is the most common cause of persistent vegetative state and severe disability in TBI [8]. Damage to the reticular activating system is proportional to the level and duration of coma noted after DAI [6]. Autonomic dysfunction symptoms seen in DAI (such as temperature control and satiety center disorders) have been associated with injury to the hypothalamus, which controls these activities [6].

In the chronic phase, DAI in milder forms can lead to residual neuropsychiatric problems and cognitive deficits, including concentration difficulties, focal neurologic lesions, memory loss, decreased attention span, intellectual decline, psychiatric disturbances, headaches, and seizures [5]. These disability symptoms are known as post-concussion syndrome [9]. DAI should be suspected in all closed head injury patients with persistent and significant impairment of consciousness in the acute phase or residual neuropsychiatric deficits in the chronic phase [5].

Disability symptoms caused by brain lesions are not usually evident in structural computed tomography (CT) or magnetic resonance imaging (MRI) [10–13]. CT may show some petechial foci of hemorrhage in the acute phase, but it underestimates DAI extent because less than 20% of DAI lesions are hemorrhagic [5]. Other radiologic features which could be appear are as follows: (1) single or multiple small intraparenchymal hemorrhages in the cerebral hemispheres (<2 cm in diameter); (2) intraventricular hemorrhage; (3) hemorrhage in the corpus callosum; (4) small focal areas of hemorrhage adjacent to the third ventricle (<2 cm in diameter); (5) brain stem hemorrhage [14]. Intraventricular hemorrhage arises from disruption of the subependymal plexus of the capillaries and veins that lie along the ventricular surface of the septum pellucidum, fornix, and corpus callosum [15].

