### Sampling

The eligibility criteria will include adult patients between 18 and 60 years who are victims of a severe (Glasgow Coma Scale ≤8) acute (hospital admission within less than 8 h from trauma) TBI and present with the DAI diagnosis. Patients younger than 18 years old will be excluded due to the known different physiopathology typical of this age. We excluded patients older than 60 because different studies revealed that these patients had a significantly worse outcome after TBI. Six months after severe head injury, 92% were dead, vegetative, or severely disabled. Four class I studies demonstrated a mortality of >75% in severely brain-injured patients older than 60. The critical age threshold for worsening prognosis appears to be above 60 in a review of class I and II studies [43].

DAI diagnosis is histopathological. It can be clinically defined by coma lasting 6 h or more after TBI, excluding cases of swelling or ischemic brain lesions [44, 45]. Focal brain injury may produce mass effects from hemorrhagic contusion or hematoma, which can induce herniation and brain stem compression, and the resultant may be coma, which is not usually immediate but develops in a secondary fashion. Otherwise, DAI can be a sole source of post-traumatic coma in the absence of mass lesions [45]. MRI will be performed in all patients for documentation. However, MRI cannot demonstrate DAI lesions in up to 10% of patients. Therefore, patients with Glasgow Coma Scale (GCS) ≤8 lasting more than 6 h without MRI or with normal CT or normal MRI will also be diagnosed as having DAI, if no other reasons justify the coma status [44–46]. Patients will be considered to have awakened from coma when they score 6 points in the best motor response in the GCS, consequently not being included in this protocol.

In summary, the inclusion criteria will be:Coma lasting more than 6 h without sedationCT scan without focal surgical lesions (Marshall I and II) and no signs of intracranial hypertensionTranscranial Doppler and optic nerve sheath US with no signs of intracranial hypertensionAdmission within less than 8 h of trauma

The exclusion criteria will be:History of drug or narcotic abuseEmergence of surgical lesions or signs of intracranial hypertension in follow-up CTsTranscranial Doppler or optic nerve sheath US presenting signs of intracranial hypertensionPsychiatric disordersInjury severity score ≥3, according to the Abbreviated Injury Scale [47]Bilateral fixed and dilated pupils

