### Sample size calculation

The previously published studies about transcranial LED therapy are case reports or case series. Besides, there is no study which evaluated transcranial LED therapy for acute severe TBI patients. Considering these facts, the sample size was calculated based on the primary outcome proportion difference (favorable vs unfavorable) on chi-square with the estimation of effect size (Cohen’s *D*) of 0.5, alpha of 5%, and statistic power of 80%. The final result was 32 patients, who will be divided into two groups (16 patients each).

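### The 30% sham rate is not justified for the patients the trial enrols, and a single 80% power hides how much depends on it: the printed 30% vs 75% gives about 76%

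*Protocol article*

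**What the plan says.** The Sample size calculation section bases the trial on a chi-square comparison of favorable against unfavorable GOSE, with an effect size "of 0.5, alpha of 5%, and statistic power of 80" percent. It concludes: "The final result was 32 patients, who will be divided into two groups (16 patients each". No outcome rates appear there.

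The rates appear only in the Discussion: "The usual result expected for severe TBI patients is about 30% of favorable outcome at 3 months". The planned effect is then given as a "difference in the favorable-outcome rate of 30% vs 75" percent.

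The Sampling section defines who is enrolled: age 18 to 60, GCS of 8 or less, a DAI diagnosis, Marshall I or II on CT, no sign of intracranial hypertension, no bilateral fixed dilated pupils, and no Abbreviated Injury Scale score of 3 or more. It gives prognosis as the reason for the age limit: "We excluded patients older than 60 because different studies revealed that these patients had a significantly worse outcome after TBI". It also requires coma of more than 6 h without sedation and leaves out patients who reach a motor score of 6.

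**The concern.** The control rate belongs to one population and the eligibility criteria describe another. For age, the protocol itself says it removes patients because they do badly, yet the comparator is described only as the rate for severe TBI patients. Nothing shows that 30% applies to the group that will be randomized.

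This matters because N is fixed and small. With 16 per arm, power depends strongly on the sham rate if the active arm is expected to reach 75% whatever the sham arm does. A reader who takes 80% at face value could read a non-significant result as evidence that the treatment failed, when the trial may have had a modest chance of detecting the planned contrast. The point would remain if the effect-size label and the mismatch between 45 and 50 points were both corrected.

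**Working it through.** **Inputs.** Effect size 0.5, alpha 5%, power 80% and 16 per arm (Sample size calculation); sham 30% and active 75% (Discussion); chi-square test (Statistical analysis). Assumed because not stated: two-sided test, no continuity correction, no dropout. The documents give no sham rate for eligible patients, so 25% to 50% is an assumed range.

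**1. The plan's own figure.** With 0.5 read as Cohen's w for a 1-df chi-square, N = (1.960 + 0.842)² / 0.5² = 31.4, so 32. Noncentral chi-square power at N = 32 is 80.7%. The stated N reproduces, and the 30% is not an input to it.

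**2. The printed rates.** w = (p2 − p1) / (2√(m(1 − m))), with m the mean of the two rates. For 30% vs 75%, m = 0.525 and w = 0.45 / (2 × 0.4994) = 0.451, below 0.5. Power at 16 per arm:
- Normal approximation: (0.45 × √16 − 1.960 × √(2 × 0.525 × 0.475)) / √(0.30 × 0.70 + 0.75 × 0.25) = (1.800 − 1.384) / 0.630 = 0.66, which is 74.5%.
- Exact (sum over all pairs of two Binomial(16, p) counts for which the Pearson chi-square exceeds 3.84): 75.8%.

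The same normal formula needs 19 per arm for 80% power.

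**3. Which way the criteria push.**
- Likely to raise the favorable rate: exclusion of age over 60, CT worse than Marshall II, intracranial hypertension, bilateral fixed dilated pupils, and an Abbreviated Injury Scale score of 3 or more.
- Likely to lower it: the requirement for coma beyond 6 h; non-inclusion of patients who reach motor score 6; and the DAI diagnosis itself, which the Background names as the leading cause of persistent vegetative state and severe disability. Both of those count as unfavorable under Outcome variables.

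The documents give no weights with which to net these.

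**4. Exact power at 16 per arm under three readings of the planned effect.** The odds ratio at 30% vs 75% is (0.75/0.25) / (0.30/0.70) = 7.

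| Sham rate | Active fixed at 75% | Odds ratio 7 held (active rate) | 45 points held (active rate) |
|---|---|---|---|
| 25% | 85% | 76% (70%) | 76% (70%) |
| 30% | 76% | 76% (75%) | 76% (75%) |
| 35% | 65% | 75% (79%) | 77% (80%) |
| 40% | 54% | 73% (82%) | 80% (85%) |
| 50% | 32% | 68% (88%) | 90% (95%) |

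Holding 45 points assumes a stronger treatment on the odds scale as the sham rate rises: at 50% vs 95% the odds ratio is (0.95/0.05) / (0.50/0.50) = 19.

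**5. What w = 0.5 requires.** Solving the formula in step 2 for the active rate gives about 80% at sham 30%, 84% at 35%, 88% at 40% and 95% at 50%.

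**The case against.** The strongest reply is that the 30% plays no part in the sample size, which rests on a generic effect size, so a wrong sham rate cannot undermine the stated 80%. The first half is correct. But the Discussion is the only place where the effect is put into outcome rates, and those rates give w = 0.451, not 0.5. The generic value also implies a sham rate: the higher that rate, the higher the active rate that 0.5 demands.

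A second reply is that the Discussion also words the effect as a difference: "we expect a treatment effect of 50 percentage points". Taken literally from 30%, that is 30% vs 80%, with exact power of 85%. So the two descriptions of the effect fall either side of 80%, and they need reconciling in any case. If a difference is what is planned, a higher sham rate does not reduce power, as the last column of the table shows. This stands, and it is why the table must state what is held fixed.

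A reader might go further and infer that eligibility removes most poor-prognosis patients, that the sham rate is therefore probably above 30%, and that power is far below what is stated. The documents do not support this:
- Criteria act in both directions, and no section quantifies either.
- The Background statement "DAI not accompanied by an intracranial mass lesion occurs in approximately 50% of patients with severe TBI and causes 35% of all TBI deaths" suggests fewer deaths in this group. But it mixes all TBI deaths with severe TBI cases, and fewer deaths do not mean more favorable outcomes if survivors are vegetative or severely disabled.
- The 92% poor outcome quoted for patients over 60 is a six-month figure, and the share of such patients behind the 30% is not given. With 8% favorable among them and an assumed share s, the rate without them is (0.30 − 0.08s) / (1 − s). That is 31% at s = 5% and 39% at s = 30%, and there is no shift if the source had already excluded them.
- The steep fall in power occurs only when the active rate is held at 75%.

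**Conclusion.** The concern holds in a limited form. The 30% is a rate for severe TBI in general and is not justified for the enrolled population; whether the true sham rate is higher or lower, and by how much, cannot be told from the documents. The one result that needs no assumption about the sham rate is that the printed 30% vs 75% gives about 76% exact power at 16 per arm, not 80%. Beyond that, for sham rates of 35% to 50%, power runs from 65% down to 32% with active fixed at 75%, from 75% to 68% with the odds ratio held, and from 77% up to 90% with the difference held. All figures assume a two-sided uncorrected chi-square and no losses. This is a weakness in how the power is justified and will be interpreted, not proof that the trial is badly underpowered.

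**What to change.** Keep N at 32. In the Sample size calculation and Discussion sections:

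- Replace the single 80% by a short table of power over sham rates of about 30% to 50%, starting with 76% at 30% vs 75%, and state for each column whether the active rate, the odds ratio or the difference is held fixed.
- If records allow, base the sham rate on the 3-month favorable proportion among the centre's past patients who would have met the Sampling criteria. Otherwise say that 30% is borrowed from severe TBI in general and that its fit to this population is unknown.
- State that a non-significant result does not exclude the planned effect.

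The cost is a count from existing records and a small table. The downside is a less favourable stated power. The test, the eligibility criteria and the conduct of the trial do not change.
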